# Efficacy of high-intensity, low-volume interval training compared to continuous aerobic training on insulin resistance, skeletal muscle structure and function in adults with metabolic syndrome: study protocol for a randomized controlled clinical trial (Intraining-MET)

**DOI:** 10.1186/s13063-018-2541-7

**Published:** 2018-02-27

**Keywords:** Metabolic syndrome, Exercise training, Interval training, Aerobic exercise, Skeletal muscle, Risk factors, Insulin resistance, Hyperinsulinemia, Glucose metabolism disorders, Myokines

## Abstract

**Background:**

Evidence of the efficacy of high-intensity, low-volume interval training (HIIT-low volume) in treating insulin resistance (IR) in patients with metabolic disorders is contradictory. In addition, it is unknown whether this effect is mediated through muscle endocrine function, which in turn depends on muscle mass and fiber type composition. Our aims were to assess the efficacy of HIIT-low volume compared to continuous aerobic exercise (CAE) in treating IR in adults with metabolic syndrome (MS) and to establish whether musclin, apelin, muscle mass and muscle composition are mediators of the effect.

**Methods:**

This is a controlled, randomized, clinical trial using the minimization method, with blinding of those who will evaluate the outcomes and two parallel groups for the purpose of showing superiority. Sixty patients with MS and IR with ages between 40 and 60 years will be included. A clinical evaluation will be carried out, along with laboratory tests to evaluate IR (homeostatic model assessment (HOMA)), muscle endocrine function (serum levels of musclin and apelin), thigh muscle mass (by dual energy x-ray absorptiometry (DXA) and thigh muscle composition (by carnosine measurement with proton magnetic resonance spectroscopy (^1^H–MRS)), before and after 12 weeks of a treadmill exercise program three times a week. Participants assigned to the intervention (*n* = 30) will receive HIIT-low volume in 22-min sessions that will include six intervals at a load of 90% of maximum oxygen consumption (VO_2_ max) for 1 min followed by 2 min at 50% of VO_2_ max. The control group (*n* = 30) will receive CAE at an intensity of 60% of VO_2_ max for 36 min. A theoretical model based on structural equations will be proposed to estimate the total, direct and indirect effects of training on IR and the proportion explained by the mediators.

**Discussion:**

Compared with CAE, HIIT-low volume can be effective and efficient at improving physical capacity and decreasing cardiovascular risk factors, such as IR, in patients with metabolic disorders. Studies that evaluate mediating variables of the effect of HIIT-low volume on IR, such as endocrine function and skeletal muscle structure, are necessary to understand the role of skeletal muscle in the pathophysiology of MS and their regulation by exercise.

**Trial registration:**

NCT03087721. High-intensity Interval, Low Volume Training in Metabolic Syndrome (Intraining-MET). Registered on 22 March 2017, retrospectively registered.

**Electronic supplementary material:**

The online version of this article (10.1186/s13063-018-2541-7) contains supplementary material, which is available to authorized users.

## Background

Metabolic syndrome (MS) is a frequent chronic condition related to physical inactivity, inadequate eating habits and obesity; MS increases the risk of type 2 diabetes mellitus and cardiovascular disease [1, 2]. The pathophysiology of MS is related to vascular and metabolic alterations, such as arterial hypertension, visceral fat accumulation, dyslipidemia, insulin resistance (IR), glucose intolerance and persistent increases in various pro-thrombotic, anti-fibrinolytic and inflammatory factors [3].

IR is a central component of MS associated with increased cardiovascular morbidity and mortality [2, 4]. IR increases the risk of diabetes (RR 6.9, 95% CI 3.7–13) and cardiovascular disease (RR 2.2, 95% CI 1.7–3.1) [4]. The increase in morbidity and mortality in patients with MS has required the application of preventive strategies and pharmacological and non-pharmacological treatment.

Aerobic exercise is a preventive and treatment strategy that reduces IR and modifies risk factors in patients with MS [5–7]. However, only half of the population complies with the current recommendation of 150 min per week of physical activity at a moderate intensity [8]. One of the main barriers to being more active perceived by people is the “lack of time” [9], which has motivated the search for the minimum amount of physical activity necessary to achieve health-related benefits and facilitate adherence [10].

High-intensity interval training (HIIT) has been used in the treatment of patients with cardio-metabolic diseases to increase adherence because it requires less volume. Compared to continuous aerobic exercise (CAE), this type of training is an effective alternative for improving maximal oxygen consumption (VO_2_ max), blood pressure, cardiac function, glucose and lipid metabolism and oxidative stress and inflammation markers [7, 11, 12]. However, the results regarding its effectiveness on IR in patients with MS and type 2 diabetes mellitus have been contradictory [6]: while one study reported greater effectiveness of HIIT than CAE in treating IR [5], others did not show differences between the two training strategies [13–15].

High-intensity, low-volume interval training (HIIT-low volume) is a type of HIIT that uses intensities close to the maximum in sessions of short duration. This training seems to generate greater local peripheral stimulation of skeletal muscle with the advantage of requiring less time and volume [11, 16, 17]. Currently, the evidence on its efficacy and safety is scarce; this evidence has been obtained from studies with quasi-experimental methodological designs that have included people without metabolic alterations, with the results obtained in response to a single exercise session or programs with duration less than 7 weeks [11, 16, 17].

Because HIIT-low volume can be demanding, not tolerable or unattractive to non-active people, training methods have been designed for high-risk populations with cardio-metabolic diseases [11, 16–18]. These methods incorporate some important elements, such as (i) decrease in the absolute intensity during the maximum load phase; (ii) increase in the stimulus duration from 30 s to 1 min; (iii) recovery periods between 1 and 2 min; and (iv) 20-min training sessions [11, 18]. With this protocol, an improvement in glucose metabolism was observed for 24 h after a two-week program in patients with diabetes mellitus [18]. Despite the short duration of the protocol, this type of training led to remodeling of the skeletal muscle and a more oxidative phenotype. It is possible that this effect was obtained by a greater muscular peripheral stimulus mediated through the peroxisome proliferator-activated receptor γ co-activator 1α (PGC-1α), a key driver of mitochondrial biogenesis and oxidative metabolism [11, 18, 19].

Among the molecular mechanisms that could explain a greater decrease in IR in response to HIIT-low volume compared to CAE are (i) a greater increase in the expression of PGC-1α; (ii) a greater increase in glucose uptake by skeletal muscle; (iii) a greater increase in the intramuscular expression of glucose transporter type 4 (GLUT-4); and (iv) greater insulin sensitivity (IS) related to greater depletion of intramuscular glycogen [6, 11, 18, 19].

Although the molecular mechanisms described could explain the greater effectiveness of HIIT-low volume compared to CAE on IR [11, 16, 18, 19], it is unknown whether the differences in this effect are mediated by the muscle endocrine function, which in turn depends on the quantity and composition of the skeletal muscle. Currently, there is some evidence that could support the potential mediating role of muscle endocrine function in the effect of HIIT-low volume on IR: (i) skeletal muscle is an endocrine organ involved in the pathophysiology of multiple chronic diseases [20, 21]; (ii) different myokines, such as irisin, myostatin, myonectin, interleukin-6 (IL-6), musclin and apelin, may be involved in IR, glucose uptake, oxidation of fats and production of hepatic glucose and lipolysis [20, 22]; (iii) lower muscle mass in the lower limbs, particularly in the thigh, is associated with MS, diabetes mellitus and increased cardiovascular morbidity and premature mortality [23, 24]; and (iv) the predominance of type II fibers observed mainly in obese people is related to IR [25].

Because exercise can decrease the expression of intramuscular musclin in murine models of IR [26], increase the serum concentrations of apelin in humans [27], and increase the muscle mass and modify the composition of the muscle fiber type towards a more oxidative phenotype [16], it is proposed that these variables may be potential mediators of the beneficial effect of HIIT-low volume on IR.

The present study aims to evaluate the efficacy of HIIT-low volume compared to CAE on IR in adults with MS and to establish whether musclin, apelin, mass and muscle fiber type of the thigh are mediators of the effect. For a hypothesis, we propose that HIIT-low volume is more effective in reducing IR and that the differences in the effect between the two training modalities are mediated by muscle endocrine function, which in turn depends on the amount and composition of fiber types.

## Methods

### Study design

A controlled, randomized clinical trial using the minimization method will be conducted, with blinding of those who will evaluate the outcomes and two parallel groups for the purpose of showing superiority. Sixty patients with MS and IR will be included and will undergo medical evaluation, laboratory tests, measurement of muscle mass and fiber type composition in the thigh, and cardio-respiratory physical capacity, both before and after 12 weeks of a treadmill exercise program. The participants assigned to the intervention will receive HIIT-low volume for 22 min, and the control group will receive CAE for 36 min three times per week. The study will be implemented and reported in line with Standard Protocol Items for Randomized Trials [28] (Fig. 1 and Additional file 1).

**Fig. 1 Fig1:**
[figure not shown]
General design of the study, schedule of enrollment, intervention and assessment*. **a** After signing the informed consent, the patients will undergo medical and biochemical evaluation. Once inclusion/exclusion criteria are verified, recruited patients will be evaluated for muscle mass, fiber type composition of the *vastus lateralis* muscle (VLM), and cardio-respiratory physical capacity. Then, patients will be assigned to a high-intensity/low-volume interval training (HIIT-low volume) or continuous aerobic exercise training (CAE) intervention. A final reevaluation will be performed. **b** Evaluations during both enrollment and close out periods are expected to last 2 weeks. The intervention will last 12 weeks. HOMA-IR, Homeostatic Model Assessment-Insulin Resistance; HbA1c, glycated hemoglobin; IR, insulin resistance; MS, metabolic syndrome

### Study site

This study will be carried out in the cardiac rehabilitation and physiotherapy section of the facilities of the outpatient clinic of the IPS-Universitaria, in Medellín (Colombia).

### Recruitment of participants

Volunteers will be recruited from the academic community of the University of Antioquia, associated institutions and in nearby communities, through messages sent by email or Facebook, posters located in various faculties, and through direct invitation to those who attend health promotion and cardiovascular prevention activities at the University. The expected time for the recruitment of participants will be 18 months. If the recruitment is slower than expected we will implement educational and communication strategies within the target populations, in order to increase the number of participants. Also, we can extend the recruitment period for another 6 months if needed. The recruitment will end once the number of required volunteers is obtained. There will be no incentives paid to participate in this study.

### Eligibility criteria

People aged between 40 and 60 years, with three criteria for MS [1], with IR according to the homeostatic model assessment (HOMA-IR) greater than 2.25 [29, 30] and with a sedentary lifestyle [31] will be included. People with a vegetarian diet, supplemental consumption of vitamin D3, injuries or musculoskeletal diseases that prevent exercise; people in a situation of physical, sensory and cognitive disability; people with a history of cardiopulmonary disease or acute or chronic inflammatory conditions, cancer, acquired immune deficiency syndrome or diabetes mellitus; and pregnant women will be excluded.

### Interventions

The training program will be controlled by physical activity specialists and will include three sessions per week of treadmill walking/running, with a progressive increase in training loads of 5% every 2 weeks and a total duration of 12 weeks.

#### High-intensity and low-volume interval training

The HIIT-low volume session will include a warm-up period of 3 min at an intensity of 30% of VO_2_ max (expressed as a measure of the external load in the speed and inclination of the treadmill), followed by six intervals that include 1 min of high intensity with a workload of 90% of VO_2_ max and 2 min with a workload of 50% of VO_2_ max. The session will end with a cooling off period of 3 min at an intensity of 30% of VO_2_ max for a total duration of 22 min (Fig. 2a).

**Fig. 2 Fig2:**
[figure not shown]
Training protocols for intervention. **a** High-intensity/low-volume interval training protocol scheme. **b** Continuous aerobic exercise protocol scheme. VO_2_ max, maximum oxygen consumption

#### Continuous aerobic exercise

The CAE session will include a warm-up period of 3 min at 30% of VO_2_ max, followed by 30 min at 60% of VO_2_ max; it will end with a cooling off period of 3 min at 30% of VO_2_ max for a total duration of 36 min (Fig. 2b).

### Adherence to the protocol

Adherence will be established from the quantification of a percentage, taking into account the total volume of physical activity performed in relation to the total volume of physical activity scheduled.

### Concomitant interventions

All people will continue with their pharmacological treatment plan and nutritional recommendations provided by the treating physician.

### Measurement of covariates and outcomes

For the collection of information, electronic formats will be designed to record the data related to each training session, the measurement of covariates and the outcomes.

#### Clinical history and physical examination

A complete clinical history will include socio-demographic information, habits and personal and family histories. Blood pressure and heart rate will be measured in the sitting and standing positions according to current recommendations [32]. For the quantification of physical activity, the Global Physical Activity Questionnaire (GPAQ) [33] validated in Colombia [34] and applied by our research group [23], will be used. The caloric intake will be estimated from the frequency of food consumption at the beginning and end of the study.

#### Anthropometry

Height will be measured with a Seca® 2013 stadiometer (Seca, Germany), and body weight will be measured with an Omron® HBF-510LA scale (Omron Healthcare, Inc., USA) with accuracy of 0.1 kg. Waist circumference will be measured with a fiberglass anthropometric tape at the intermediate point between the lower edge of the last rib and the iliac crest, in the horizontal plane. The perimeter of the thigh will be measured 1 cm below the gluteal fold, perpendicular to the longitudinal axis of the thigh. Body mass index (BMI) will be calculated with the formula weight (kg)/height (m)^2^.

#### Cardio-respiratory physical capacity

VO_2_ max will be measured directly with an open circuit spirometer Oxycon Delta by Jaeger® (VIASYS Healthcare GmbH, Germany) and a treadmill. An exercise physiologist will monitor the test, and the electrocardiogram and heart rate will be recorded continuously. Participants will initially warm up for 3 min, walking at a speed of 3.5 miles per hour, with an inclination angle of 1%. Then, the speed of the treadmill will increase 0.5 miles per hour every minute until exhaustion. It will be considered a maximum test when (i) a plateau in VO_2_ despite an increase in work or a respiratory quotient equal to or greater than 1.10 are observed; and (ii) the participants reach the expected maximum heart rate.

#### Lipid profile and glycosylated hemoglobin

A venous blood sample will be obtained after a fast of 8–12 h to measure the total cholesterol, high-density lipoprotein cholesterol (HDL), plasma triglycerides and glycosylated hemoglobin, using standardized procedures.

#### Insulin resistance

HOMA-IR will be used to estimate IR, insulin sensitivity (IS) and the percentage of functioning pancreatic β cells (% β) [35]. HOMA-IR will be calculated before and between 44 and 48 h after the last session of the exercise training program, from the blood glucose and insulinemia values obtained from a venous blood sample taken after fasting for 8–12 h [35]. The measurement of insulinemia will be performed with the sandwich immunoassay technique with direct chemiluminescence technology with an ADVIA Centaur® CP Immunoassay System (Siemens, Germany).

#### Quantification of serum levels of musclin and apelin

Concentrations of musclin and apelin will be measured in serum using a sandwich-type enzyme linked immunosorbent assay kit (Human Musclin ELISA kit, LifeSpan BioSciences Inc., Catalog number LS-F7799, USA; Human Total Apelin ELISA kit, MyBioSource, Catalog No. MBS-725907, USA). Samples will be taken before and between 44 and 48 h after the last exercise session. Initially, the samples will be stored at − 80 °C, and then for the assay, they will be thawed, and 100 μL will be applied in duplicate to the wells of the ELISA kit. The samples will be incubated at 37 °C; subsequently, the secondary antibody conjugated to biotin will be applied; finally, the samples will be incubated with avidin coupled to an enzyme with peroxidase action. The optical density of each well will be determined in an ELISA reader (Thermo Scientific Varioskan Lux, USA) at 450 nm. The final values will be reported in picograms/milliliter of musclin and apelin.

#### Measurement of muscle mass

This step will be performed at the beginning and at the end of the exercise training program, within the first 96 h after the last session, by employing the dual energy x-ray absorptiometry (DXA) technique using a Discovery Wi DXA system® (Hologic, USA) and the Hologic APEX v4.5.3 program (Hologic, USA). The measurement of thigh muscle mass will be made on the right side according to the technique described by Visser and defined by an area located between two horizontal lines located at the lowest point of the ischial tuberosity and at the knee joint as the upper and lower limits, respectively [36].

#### Evaluation of the fiber type composition of the right *vastus lateralis*

The estimation of the proportion of the area occupied by type II muscle fibers will be made at the beginning and the end of the exercise training program in the first week after the last session, based on the quantification of carnosine in the right *vastus lateralis* muscle (VLM) using the proton magnetic resonance spectroscopy technique (^1^H–MRS) [37] and a flexible coil according to the technique standardized by our group to evaluate body segments of large muscle mass [38], in turn modified from Baguet’s technique [37]. A three-Tesla Magnetom Skyra magnet, with a Flex Large 4A3T coil interface and the SyngoMR D13 program (Siemens, Germany), will be used. Each person will be placed in the supine position on the spectroscopy table, with the lower limbs extended and supported on a 5-cm cushion in the popliteal region. The largest mass of the VLM will be sought in the area between the middle of the externally facing right thigh and the middle third and distal junction of the same thigh; these anatomical points will be indicated with vitamin E capsules. A voxel of 10 × 15 × 35 mm will be positioned in the most voluminous region of the muscle, in the area delimited by the capsules, using a T1-weighted gradient-echo sequence in the three planes, with 5 mm sections and repetition time (RT)/echo time (ET) = 250/2.52 ms. The acquisition of the spectra will be performed using a point-resolved single voxel spectroscopy (PRESS) sequence with and without water saturation to evaluate the carnosine and water signals, respectively. For the processing of the signals and the absolute quantification of carnosine, the jMRUI 5.1 program (Autonomous University of Barcelona, Spain) will be used, with phase correction, Gaussian apodization, adjustment of the water reference to 4.7 ppm and subtraction of water, lipids and other metabolites within the signal.

### Sample size

A total required sample size of 30 people in each group was calculated assuming an IS increase of 10% [39], 15% standard deviation [5], a 95% confidence level, 80% power, a 1:1 ratio, and a dropout rate of 5%. In addition, a correlation coefficient of 0.44 between the baseline and final IS values was taken into account [40].

### Random assignment, implementation and masking

The Coordinating Center of the SICOR Clinical Trial, external to the group of researchers, will perform the randomization at a ratio of 1:1 (HIIT-low volume, *n* = 30; CAE, *n* = 30), with the minimization method [41] with Minimpy® software, version 0.3 [42], taking into account the values of the following variables: age (< 50 and ≥ 50 years), gender (male and female) and BMI (< 30 and ≥ 30 kg/m^2^). A base probability of 0.7 will be used under the “bias coin” method and variance as a measure of the imbalance distance between the groups, for the inclusion of the next participant [43].

The communication between the researchers who will perform the intervention and the center responsible for the assignment to the treatment groups will be conducted by telephone to guarantee independence. The measurement of outcomes will be carried out by evaluators who will not know the assignment of patients to the treatment groups. Two researchers will feed a database based on information recorded in formats at each training session, with the measurement of covariates and outcomes. The files of the participants will be stored in numerical order in a safe place and will be accessible through a password. A code will be used that will prevent identification of the patient and that, in turn, will not be visible to the person performing the statistical analysis.

### Statistical analysis

Initially, an exploratory analysis of the data will be carried out, and the Shapiro-Wilk test will be used to evaluate if the quantitative variables come from a population with a normal distribution. The mean and the standard deviation, the median and the interquartile range and the percentage will be used for the description of the socio-demographic, clinical, anthropometric and physiological variables of the included persons.

Both intention-to-treat and by-protocol analyses will be carried out; the latter will consider those patients who had adherence higher than 80%. The multiple imputation method (10 imputations) will be used to manage missing data based on age, gender, BMI and baseline VO_2_ max [44].

Analysis of covariance (ANCOVA) will be used [45] to estimate the effect of HIIT-low volume compared to CAE on IR, IS, percentage of pancreatic β-cell functioning, plasma levels of musclin and apelin and mass and composition of thigh muscle by fiber type at the end of the intervention. The assumptions of homogeneity of variance will be assessed with the Levene F test and the linearity and homogeneity of the slopes. If the assumptions are not met, a logarithmic transformation will be performed, or the Box-Cox procedure will be used. The variables used in the minimization procedure (age, gender and BMI) will be included in the analysis according to the current recommendations [41]. A re-randomization test will be performed using permutations for inference purposes [41].

To establish if the musclin, apelin, muscle mass and fiber type composition of the thigh mediate the effect of training on IR, a theoretical model was proposed to estimate the total, direct and indirect effects and the percentage explained by the mediator (Fig. 3). A model of structural equations will be used with the “path analysis” technique and basic principles proposed in the context of clinical trials [46–48]. A statistical significance level œ = 0.05 will be established, and STATA, version 14.0, and IBM SPSS Statistics, version 21.0, will be used.

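### The imputation model as listed omits the randomised arm and the baseline outcome: omitting arm shrinks a true intention-to-treat difference by about the missing fraction, and omitting baseline costs precision

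*Protocol article*

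**What the plan says.** All but one of the relevant statements are in the Statistical analysis section of the protocol article.

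- Method: multiple imputation, with 10 imputations, will be "used to manage missing data based on age, gender, BMI and baseline VO_2_ max". Nothing else in the article adds treatment group or baseline outcome, or says that imputation is done within arm.
- Analysis model: "Analysis of covariance (ANCOVA) will be used [45] to estimate the effect of HIIT-low volume compared to CAE on IR, IS", together with β-cell function, the myokines, and thigh muscle mass and composition.
- Covariates: "The variables used in the minimization procedure (age, gender and BMI) will be included in the analysis".
- Inference: a re-randomization test using permutations is announced.
- The Sample size section adds that "a correlation coefficient of 0.44 between the baseline and final IS values was taken into account". ANCOVA is therefore meant to draw on the baseline value.

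**The concern.** An imputation model should contain at least the variables of the analysis model that uses the imputed data. Here the analysis estimates a difference between arms, yet the listed imputation variables carry no information about arm. Imputed final values have the same expected value in both arms for given age, gender, BMI and VO2 max, so they dilute any true difference. The list also lacks the one predictor whose correlation with the final value the article reports.

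At stake are the size of the intention-to-treat estimate for insulin resistance and the other ANCOVA outcomes, and the width of its interval. If the same imputed data sets feed the path analysis, the direct and indirect effects could be affected too.

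**Working it through.** **Inputs.** From Sample size: a 10% increase in insulin sensitivity, standard deviation 15%, 95% confidence (taken as two-sided alpha 0.05), 80% power, 1:1 ratio, dropout 5%, correlation 0.44. From Statistical analysis: 10 imputations and the four listed variables. From Trial status: 19 finished and one withdrew, so 1/20 = 5% of those whose outcome is known. The 10% is read as a between-group difference of 10 points.

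**The plan's own figure first.** n per group = 2 × (1.960 + 0.842)² × (15/10)² = 35.32. Multiplied by 1 − 0.44² = 0.8064 this is 28.48. Divided by 0.95 it is 29.98, so 30 per group. The stated size is reproduced, and it relies on baseline adjustment.

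**Expected shrinkage.** If a fraction p of each arm is missing completely at random and imputed without arm, the expected difference is (1 − p) × Δ + p × 0. With Δ = 10 this is 9.5 at 5%, 9.0 at 10% and 8.0 at 20%.

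**Simulation.** 30 per arm, difference 10, SD 15, correlation 0.44, missing completely at random, 10 proper imputations, Rubin's rules, ANCOVA on arm, baseline, age, gender and BMI; 1,500 trials per row, Monte Carlo error about 0.1. Only the 5% row is the plan's own rate; the others are assumptions. Mean estimates:

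| Missing, HIIT + CAE | Four listed | + arm only | + baseline only | + both | Complete-case ANCOVA |
|---|---|---|---|---|---|
| 2 + 1 (5%) | 9.59 | 10.12 | 9.60 | 10.15 | 10.13 |
| 3 + 3 (10%) | 8.85 | 9.91 | 8.84 | 9.90 | 9.90 |
| 6 + 6 (20%) | 7.78 | 9.87 | 7.72 | 9.87 | 9.85 |

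Relative to complete cases the listed model gives 9.59/10.13 = 0.95, 8.85/9.90 = 0.89 and 7.78/9.85 = 0.79, close to 1 − p. Adding arm alone removes the shrinkage; adding baseline alone does not.

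**Interval width.** The mean Rubin standard error is 3.82, 4.02 and 4.39 with the listed variables, against 3.72, 3.85 and 4.17 with both added. The actual spread of the listed-variable estimates is about 0.09 × √1,500 = 3.5 in each row (3.3 to 3.7 allowing for rounding of 0.09). The reported error is too large for the estimate it accompanies.

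**No true difference, 10% missing completely at random.** The listed model gives a mean of −0.09 (no bias within error) and rejects in 2.7% of trials, which is conservative.

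**Role of the baseline outcome.** With arm in the model and data missing completely at random, adding baseline lowers the standard error from 3.78 to 3.72, 3.97 to 3.85 and 4.39 to 4.17. Suppose instead that about 10% are missing and that missingness depends on baseline in opposite directions in the two arms (an assumption). With arm but not baseline, a true 10 then becomes 9.10 or 10.95, depending on the direction; with both it is 9.94 or 10.13. With no true difference, the four listed variables give −0.77 or +0.92, against −0.08 or +0.22 with both.

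**Power, by test.** Rejection rates at 5%, 10% and 20% missing:

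| Imputation and test | 5% | 10% | 20% |
|---|---|---|---|
| Four listed, Rubin's rules | 70% | 59% | 38% |
| Four listed, permutation of arm | 74–77% | 70% | 61–62% |
| Both added, Rubin's rules | 75–76% | 71–73% | 64–65% |

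Ranges cover repeat simulations. The permutation rows re-assign arm by simple permutation and use the mean ANCOVA estimate across imputations. This is one plausible version of the planned test; it does not replay the minimization.

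**The case against.** The strongest reply is that this is one sentence in a condensed article, which does not say that the list is exhaustive or that imputation ignores arm. That stands as a condition: the bias follows only if the list is the model. But the article fixes both the number of imputations and the predictors, so the text needs correcting even if the working code already includes arm.

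The second reply concerns size. At the plan's 5% dropout, which the withdrawals so far match, the shrinkage is about 0.5 of 10 points, well inside one standard error. This also stands.

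The third concerns power. A reader might take the Rubin's-rules rates as the power this trial would lose. The article names a re-randomization test for inference, and under a permutation reference most of that loss disappears. What remains is the shrunken estimate and the overwide Rubin interval. Arm-free imputation also has one convenience: it need not be repeated at each re-assignment.

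Other stronger readings are tempting but unsupported:

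- That every imputed value pulls towards zero. Imputed values are random draws; the shrinkage is an average and needs a true difference.
- That the missing baseline outcome is part of the attenuation. Adding it alone changes nothing there.
- That the harder regimen will lose more people. The article gives no dropout by arm.
- That indirect effects will be attenuated. The article does not say how missing data enter the path analysis.

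**Conclusion.** The point holds in a limited form. Read literally, the listed imputation model biases the intention-to-treat estimate towards zero whenever the arms truly differ, by about the missing fraction: roughly 0.5 of 10 points at 5%, and 1 to 2 points at an assumed 10% to 20%. Rubin's-rules intervals are too wide for that estimate. The cause is the absent arm term. The absent baseline outcome is a separate fault: it costs precision, with possible bias of either sign if dropout depends on baseline differently by arm.

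A false superiority claim is not made more likely when data are missing completely at random, and the planned re-randomization test protects most of the power. The figures assume normal outcomes, the Sample size inputs read as a between-group difference, and an ANCOVA that adjusts for the baseline outcome. The article implies that adjustment through its correlation but does not name the covariate. The planned 30 per group is unaffected.

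**What to change.** Amend the imputation sentence to say that missing outcomes will be imputed from treatment group, the baseline value of that outcome, age, gender, BMI and baseline VO2 max. Imputing separately within each arm is an acceptable alternative to the treatment-group term. If the same imputations feed the path model, include the mediators and HOMA-IR as well. State also how the imputations combine with the re-randomization test.

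All these variables are already collected and the sample size does not change. The one real cost is computing time: with arm in the imputation model, the re-randomization test should repeat the imputation under each re-assignment.
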